## Abstract

**Background:**

Fluid bolus administration is widely recommended as part of the initial treatment of paediatric sepsis, though the physiological benefits and harms are unclear. The primary aim of this study is to determine the effect of fluid bolus administration on cardiac index (CI). Secondary aims are to determine the effect of fluid bolus administration on extra-vascular lung water (EVLW), whether fluid responsiveness can be predicted by inferior vena cava (IVC) collapsibility, and whether fluid responsiveness correlates with changes in vital signs.

**Methods/design:**

A prospective observational study of children presenting to the Emergency Department of The Royal Children’s Hospital with clinically diagnosed sepsis requiring fluid bolus administration. Prior to fluid bolus administration, an echocardiogram, lung ultrasound, and IVC ultrasound will be performed, and vital signs recorded. These will be repeated 5 min after and 60 min after fluid bolus administration. Recorded echocardiograms and lung/IVC ultrasound will be evaluated independently by a paediatric cardiologist and paediatric emergency physician, respectively, blinded to the patient identity and time of examination relative to time of fluid bolus administration. Fifty patients will be enrolled in the study based on a precision based sample size calculation. Results will be analysed for change in CI and change in EVLW 5 min after and 60 min after fluid bolus administration compared to baseline, IVC collapsibility as a predictor of fluid responsiveness, and the relationship between fluid responsiveness and changes in vital signs.

**Discussion:**

This study will explore assumptions about the effect of fluid boluses on CI in children with sepsis, and will provide evidence for secondary effects on other organ systems. This may lead to novel methods for assessment and decision making in the initial resuscitation of paediatric sepsis in clinical and research settings, and will likely influence the design of future interventional studies in this arena.

**Trial registration:**

The study is registered with the Australian and New Zealand Clinical Trials Registry (ACTRN12614000824662; 04 August 2014).

## Background

Sepsis is the final common pathway and mode of death for many paediatric infectious processes, globally accounting for over 6 million childhood deaths per year, mostly in underdeveloped countries [1]. Case fatality rates are 5–10 % in industrialised countries, and 20–30 % in low and middle income countries [2, 3]. Despite being common and serious, the therapies for the initial resuscitation of paediatric sepsis are based on little or no evidence. In particular, fluid resuscitation therapy (FRT) is widely recommended for initial sepsis resuscitation [4, 5], but there is limited understanding of its potential beneficial and harmful effects, how the balance of benefits and harms may be influenced by patient and disease factors, and how this balance may be incorporated into treatment guidelines for translation into clinical use.

Fluid resuscitation was initially described in patients with severe dehydration during cholera epidemics in the early 19^th^ century [6], and subsequently applied to trauma patients with haemorrhagic shock [7]. Both of these disease states are characterised by intravascular volume depletion, and replacement of this intravascular volume with the same type of fluid that was lost helps to restore homeostasis. Fluid resuscitation for sepsis was popularised in 2001, when early goal-directed therapy (EGDT) was shown to improve survival in adults with septic shock when instituted in the emergency department (ED) [8]. This approach involved aggressive fluid resuscitation to achieve threshold central venous pressure (CVP) values, followed by early initiation of vasoactive agents for ongoing hypotension, and transfusion of blood for low central venous oxygen saturations (ScvO2). As the initial therapy in EGDT, aggressive fluid resuscitation was the most commonly applied in practice, and the foundation upon which subsequent therapies were based. Since the publication of the EGDT protocol, the harms from aggressive fluid resuscitation and cumulative positive fluid balance have become apparent [9–16], and the benefit of EGDT compared to standard care has been called into question [17–19]. In particular, the Fluid Expansion As Supportive Therapy (FEAST) study found that FRT in Sub-Saharan African children with fever and signs of poor perfusion increased mortality compared to no FRT [20]. This raises serious questions about the role of FRT in the management of sepsis, and our understanding of the pathophysiological mechanisms underlying FRT in conditions where no volume loss has occurred.

Aggressive FRT with the aim of increasing stroke volume, with the assumption that this will improve end-organ perfusion and cellular oxygen use, may be physiologically flawed [21]. FRT into high-capacitance veins may in fact increase cardiac filling pressures faster than venous pressure due to limited diastolic compliance of the heart, thus reducing the pressure gradient driving venous return [22–24]. Increased venous pressure following FRT may reduce the gradient driving vital organ perfusion (MAP-CVP) [25]. Microcirculatory dysfunction through damage to the endothelial glycocalyx may be mediated partly by natriuretic peptides released as cardiac filling pressures increase following FRT [26–30]. The net effect of FRT in sepsis may be that it contributes significantly to end-organ oedema and dysfunction, and the progression from SIRS to multi-organ dysfunction and death [9, 10, 12, 13, 31, 32].

Limited published literature on the effect of FRT on cardiac output (CO) suggests that any effect is modest and transient. In a study of 20 adults with circulatory shock, the mean increase in CO immediately following FRT was 16 %, which decreased to 6 % above baseline after sixty minutes [33]. In a separate study, 32 adults with septic shock were found to have a mean increase in CO of 15 % immediately after FRT, which returned to 3 % above baseline 40 min after FRT (*p* < 0.001) [34]. There is no published literature on the effect of FRT on cardiac index (CI = CO/body surface area (BSA)) in children. The ability to predict the response to FRT allows the clinician to restrict this therapy only to those that are fluid responsive. Fluid responsiveness is considered an increase in cardiac output of 10-15 % in response to a fluid challenge (250–500 ml in adults) [35]. In the undifferentiated adult ICU population, as few as 50 % of patients may be fluid responsive [35]. The remainder receive all of the potential harms from FRT with none of the potential benefits. IVC ultrasound is a dynamic method for assessing fluid responsiveness using cardiopulmonary interactions [36]. In spontaneously ventilating adults, IVC collapsibility of >40 % has been shown to be predictive of fluid responsiveness, while IVC collapsibility of <15 % is predictive of being fluid unresponsive [37]. No study has validated IVC collapsibility as a predictor of fluid responsiveness in children.

We set out to determine the effect of FRT on CI 5 min after and 60 min after fluid bolus administration in paediatric sepsis. Secondary aims include: the effect of FRT on extra-vascular lung water (EVLW), whether fluid responsiveness can be predicted by inferior vena cava (IVC) collapsibility, and whether fluid responsiveness correlates with changes in vital signs.

## Methods/design

### Study design and setting

The study is designed as a prospective observational study of children with sepsis. It will be conducted at a single paediatric ED in The Royal Children’s Hospital (RCH), Melbourne, Australia. RCH is a tertiary children’s hospital with an annual ED census of >85,000 children less than 18 years of age.

### Inclusion and exclusion criteria

Inclusion and exclusion are listed in Table 1. Inclusion criteria are based on international consensus definitions for the diagnosis of sepsis in children [38].

**Table 1 Tab1:** Inclusion and exclusion criteria

Inclusion criteria- all of: Suspected infection Temperature >38 °C or <36 °C Systemic Inflammatory Response Syndrome Tachycardia (temperature corrected heart rate >2 SD above normal for age^a^) *or* Tachypnoea (respiratory rate >2 SD above normal for age) Plan to administer a standardised fluid bolus by the treating clinician Standardised fluid bolus: 20 ml/kg of 0.9 % saline administered via manual push/pull or pressure bag (NOT by infusion pump). Exclusion criteria- any of: Underlying uncorrected structural cardiac disease Non-curative goals of therapy Non-English speaking	

^a^heart rate was corrected by 10 beats per minute for every degree celcius above 38^o^ [55]

### Study procedure

Patients who fulfil the eligibility criteria and whose parents provide written informed consent will be entered into the study. Prior to administration of a standardised fluid bolus, transthoracic echocardiography, lung and IVC ultrasound will be performed, and vital signs recorded (Fig. 1). Five minutes and 60 min after administration of a standardised fluid bolus, the same measurements will be taken. All ultrasound measurements will be taken by the Principal Investigator (PI), who has a Post Graduate Certificate in Echocardiography through The University of Melbourne, Australia. Recorded echocardiograms will subsequently be assessed by a blinded paediatric cardiologist. Lung ultrasound and IVC ultrasound will be assessed by a blinded paediatric emergency physician with a Diploma in Diagnostic Ultrasound (Australian Society for Ultrasound in Medicine). Vital signs that will be recorded from the patients monitor (Phillips MP70, Phillips Healthcare, Andover, MA) include: heart rate (HR), respiratory rate (RR), blood pressure (BP), and peripheral oxyhaemoglobin saturation (SpO2). Additionally, patient temperature in degrees celcius will be recorded and a 10 s video recording of the patient will be taken at each time point and used to assess conscious state, capillary refill, and respiratory effort. These video recordings will be scored in terms of Glasgow Coma Scale for conscious state, time in seconds for capillary refill, and Silverman Score for respiratory effort [39] by a blinded paediatric emergency physician. Final outcomes will be obtained from the patient medical record following discharge or death.

**Fig. 1 Fig1:**
[figure not shown]
Schedule of observations recorded during the 60 min study period. *a standardised fluid bolus was defined as 20 ml/kg of 0.9 % saline

### Study flow chart

#### Outcome measures

*The primary outcome measure* is the percentage change in CI 5 and 60 min after standardised fluid bolus administration compared to baseline.

*Secondary outcome measures* include the change in EVLW after standardised fluid bolus administration, whether IVC collapsibility is predictive of fluid responsiveness, and whether the observed change in cardiac output following standardised fluid bolus administration is correlated with changes in vital signs and clinical observations. We also collected the following outcome data: ICU admission, requirement for inotrope/vasopressor infusion, requirement for non-invasive or invasive ventilation, requirement for renal replacement therapy, requirement for extracorporeal membrane oxygenation (ECMO), final microbiological diagnosis, and mortality.

### Ultrasound techniques

*Cardiac index* will be measured by trans-thoracic echocardiography using a Zonare Z.one (Zonare Medical Systems, Mountain View, CA, USA) and a 3–10 MHz phased array (cardiac) transducer. An apical 5 chamber view of the heart will be obtained and the left-ventricular outflow tract visualised. A 3 mm pulsed-wave doppler sample volume will be gated at the level of the aortic valve and the resulting waveform recorded. The mean velocity-time integral (VTI) over three respiratory cycles will be recorded as the final VTI measurement. Left-ventricular outflow tract (LVOT) diameter will be measured from a parasternal long-axis (PLAX) view in systole. Stroke volume will be calculated as (πr^2^) x velocity-time integral (VTI), and CO as stroke volume SV x HR. CI will be calculated as CO/BSA. Attempts to minimise the impact of inter and intra-observer variability on the study results include: blinding of the ultrasound assessor to the patient identity and timing of the study relative to the timing of fluid bolus administration; and assessment of intra and inter-rater reliability between the PI and the PI and blinded assessor, respectively, for all ultrasound-based assessments.

*Extravascular lung water* will be measured on lung ultrasound using a Zonare Z.one and an 5–14 MHz linear array probe set at a depth of 5 cm. Eight views will be obtained and recorded as described in the Fluid Administration Limited by Lung Sonography (FALLS) protocol [40]. Lung ultrasound cine-loops will be scored in a blinded fashion for the presence of B-lines, confluent B-lines, or complete loss of lung aeration, and used to calculate a lung ultrasound score [41, 42].

*Inferior vena cava collapsibility* will be measured using a Zonare Z.one and a 1–4 MHz curved array transducer. A sub-costal long-axis view of the IVC will be obtained including the IVC-right atrial (RA) junction and confluence of the hepatic veins [43]. A cine-loop recording will be taken over 3 respiratory cycles. IVC collapsibility will be measured at the level of the hepatic veins at end-inspiration and end expiration [44]. IVC collapsibility will be calculated as: maximum - minimum diameter/minimum diameter x 100.

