### Sample size, power, and statistical methods

For a precision based sample size estimation based on the continuous outcome variable of change in cardiac output following standardised fluid bolus administration, the following assumptions have been made: a mean increase in cardiac output of 20 % with a standard deviation of 10 %, a precision of the study tool (echocardiogram) of +/− 2 %. For a precision estimate of 5 %, a sample size of 50 would be required. This would also allow for regression analysis of several suspected confounding variables, including age, underlying illness aetiology (respiratory vs non-respiratory), and total volume of fluid previously administered.

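### IVC collapsibility is defined with the minimum diameter as denominator, so the index has no upper limit and is undefined when the vein collapses fully

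*Protocol article*

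**What the plan says.** The Ultrasound techniques section gives the only formula for this index in the article: "IVC collapsibility will be calculated as: maximum - minimum diameter/minimum diameter x 100". On how the diameters are obtained, it says "IVC collapsibility will be measured at the level of the hepatic veins at end-inspiration and end expiration", from a cine-loop over three respiratory cycles.

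The index serves a secondary outcome, stated under Outcome measures as "whether IVC collapsibility is predictive of fluid responsiveness". No cut-off is named there.

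The Background supplies adult context: "In spontaneously ventilating adults, IVC collapsibility of >40 % has been shown to be predictive of fluid responsiveness". A second, lower figure of <15 % is given there as the mark of adults who do not respond to fluid. Neither figure comes with a formula or denominator. The Background then notes: "No study has validated IVC collapsibility as a predictor of fluid responsiveness in children".

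**The concern.** A percentage called collapsibility would naturally be the share of the maximum calibre that is lost during the breath, running from 0 % (no change) to 100 % (full collapse). The printed formula instead divides the loss by the diameter that remains. As the vein collapses the denominator shrinks towards zero, so the index grows without limit and then cannot be computed.

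This would not be a random loss of data. The failure falls at the high end of the predictor, where the Background's reasoning places the children most likely to respond to fluid. In a study of 50 children, a few values that are extreme or missing for this reason could distort the answer to the secondary question. The same section promises intra- and inter-rater reliability for all ultrasound assessments, and on this scale a few nearly collapsed veins could drive those statistics.

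**Working it through.** The plan gives no numerical result for this index, so there is no figure to reproduce. The check is algebra on the printed formula.

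**Inputs.** The formula (Ultrasound techniques) and the adult figures of 40 % and 15 % (Background, denominator not stated). The diameters in the examples are illustrative.

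**1. Brackets.** By the usual order of operations, the printed line is maximum - (minimum/minimum) x 100 = maximum - 100. For a maximum of 10 mm and a minimum of 6 mm this is -90. Nobody would compute that, so the missing brackets are a typographic slip. The intended reading must be D = (max - min)/min x 100.

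**2. Relation to loss of calibre.** Let C = (max - min)/max. Then min = max(1 - C), so, as fractions, D = C/(1 - C) and C = D/(1 + D). For 10 mm and 6 mm, C = 4/10 = 40 % and D = 4/6 = 66.7 %.

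**3. Range of the printed index.**

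| Calibre lost, C | Printed index, D |
|---|---|
| 15 % | 0.15/0.85 = 17.6 % |
| 40 % | 0.40/0.60 = 66.7 % |
| 50 % | 0.50/0.50 = 100 % |
| 80 % | 0.80/0.20 = 400 % |
| 90 % | 0.90/0.10 = 900 % |
| 99 % | 0.99/0.01 = 9900 % |
| 100 % | division by zero |

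**4. Sensitivity to measurement error.** The slope of D in C is 1/(1 - C)². At C = 0.80 it is 1/0.04 = 25. For a 5 mm vein, reading the minimum as 0.5 mm instead of 1.0 mm moves D from 4.0/1.0 = 400 % to 4.5/0.5 = 900 %. On the maximum-diameter scale the same change is 4.0/5 = 80 % to 4.5/5 = 90 %.

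**5. What survives.** D rises strictly with C for C below 100 %, so the ranking of children is the same on either scale. In a check on 50 simulated children, none fully collapsed, the ROC area was 0.544 for both indices. Their linear correlation in that sample was only 0.78, so statistics that use the values themselves are not invariant.

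**6. The adult figures.** Two cases, since the documents do not settle the denominator:

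- If they use the maximum diameter (assumption), 40 % and 15 % correspond to 66.7 % and 17.6 % on the printed index.
- If they use the minimum diameter, there is no shift on the printed index, but on the maximum-diameter scale they become 0.40/1.40 = 28.6 % and 0.15/1.15 = 13.0 %.

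**The case against.** The best defence is that little of the secondary question depends on the scale. Because the index preserves rank, discrimination by ROC area is the same, a fully collapsed vein can be ranked highest, and a cut-off found on one scale converts exactly to the other. The primary outcome and the sample size do not involve the index. The cine-loops are recorded, so correction is possible later without loss of data. The minimum in the denominator may itself be a slip of the pen, like the missing brackets. Nearly all of this stands, and it limits the severity. It does not rescue the printed rule: the article gives no instruction for ranking full collapse, and the formula returns no value there.

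A reader might also infer that the study's index is on a different scale from the >40 % and <15 % figures, and that children would be misclassified when those cut-offs are tested. The documents do not support this. The Background gives no denominator for the figures, and the cited source is not at hand. The figures appear only as adult context; the outcome is prediction in general, and nowhere does the article plan to classify children at 40 % or 15 %. Nor does it describe a regression on this index: the one regression it mentions concerns age, illness aetiology and previous fluid volume.

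**Conclusion.** The formula is wrong as written. From the printed text alone, once the brackets are supplied, the index passes 100 % when the vein loses more than half its calibre, reaches 400 % at 80 % loss, magnifies small errors in the minimum diameter, and is undefined at full collapse.

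The consequence is confined to one secondary outcome. It bears on any analysis that uses the values themselves, and on a rank-based analysis only if fully collapsed veins are dropped. How many children would be affected cannot be derived from the documents.

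A mismatch with the adult figures is possible but not established: it depends on an unstated denominator. Severity: should-fix.

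**What to change.** Replace the formula with: IVC collapsibility (%) = [(maximum diameter - minimum diameter) / maximum diameter] x 100. This runs from 0 to 100 % and gives 100 % at full collapse, so no child is lost for that reason.

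State in the Background which formula underlies the >40 % and <15 % adult figures, and compare the study's results with them only on a matching scale. If they turn out to use the minimum diameter, convert them (to 28.6 % and 13.0 %) before any comparison with the corrected index.

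The cost is one line for the formula and one sentence for the adult figures. Both diameters are already measured, so no new data are needed and nothing else in the design changes.

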### Sample size, power, and statistical methods

For a precision based sample size estimation based on the continuous outcome variable of change in cardiac output following standardised fluid bolus administration, the following assumptions have been made: a mean increase in cardiac output of 20 % with a standard deviation of 10 %, a precision of the study tool (echocardiogram) of +/− 2 %. For a precision estimate of 5 %, a sample size of 50 would be required. This would also allow for regression analysis of several suspected confounding variables, including age, underlying illness aetiology (respiratory vs non-respiratory), and total volume of fluid previously administered.

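### The sample size of 50 does not follow from the stated SD of 10 %, precision of 5 % and echocardiogram precision of +/- 2 %

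*Protocol article*

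**What the plan says.** The section on sample size, power and statistical methods opens: "For a precision based sample size estimation based on the continuous outcome variable of change in cardiac output". It then lists its assumptions:

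- "a mean increase in cardiac output of 20 % with a standard deviation of 10" %;
- "a precision of the study tool (echocardiogram) of +/− 2" %.

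The target and result follow: "For a precision estimate of 5" %, "a sample size of 50 would be required". The Methods/design part of the Abstract relies on this result: "Fifty patients will be enrolled in the study based on a precision based sample size calculation".

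The article gives no formula, confidence level or dropout allowance for the calculation. It does not say whether 5 % is a half-width or a full width, or how the +/- 2 % enters.

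Under Outcome measures, the primary outcome is the percentage change in cardiac index (CI) from baseline at both 5 and 60 minutes. The sample-size paragraph names no time point. In the Background, one adult study is reported thus: "the mean increase in CO immediately following FRT was" 16 %, falling to 6 % above baseline at sixty minutes. A second adult study found 15 % immediately and 3 % at 40 minutes.

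**The concern.** This calculation is the only quantitative basis given for the size of the study, and the standard formula for the precision of one mean does not return 50 from its inputs. On the most natural reading, +/- 5 points at 95 % confidence, 50 is about three times what the inputs call for.

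The reader therefore cannot tell what precision the study will have. That matters most at 60 minutes, where the cited adult data suggest a small residual change. An interval of +/- 5 points and one of +/- 2.8 points differ in whether a change of about 3 or 4 points can be told from zero.

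**Working it through.** **Inputs from the sample-size section:** SD 10 percentage points; target precision 5; tool precision +/- 2; stated n = 50. The mean of 20 % does not enter a formula for absolute precision.

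**Assumed because not stated:** two-sided 95 % confidence and no dropout. 90 % and 99 % confidence are shown as the range.

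**Formula for one mean:** n = (z × SD / h)², rounded up, where h is the half-width. The t version replaces z by the t quantile on n − 1 degrees of freedom and is solved by iteration.

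**Step 1: attempt to reproduce 50 from SD 10 and precision 5.**

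- Half-width 5 at 95 %: (1.96 × 10 / 5)² = 15.4, so 16 (t: 18).
- Full width 5, so h = 2.5, at 95 %: (1.96 × 10 / 2.5)² = 61.5, so 62 (t: 64).

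| Confidence | 5 % as half-width (z / t) | 5 % as full width (z / t) |
|---|---|---|
| 90 % | 11 / 13 | 44 / 46 |
| 95 % | 16 / 18 | 62 / 64 |
| 99 % | 27 / 31 | 107 / 110 |

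None of these is 50. Reading 5 % as relative to the mean of 20 % (h = 1 point) gives 385 at 95 %. Working backwards with z at 95 %, n = 50 needs an SD of 5 × √50 / 1.96 = 18.0 for half-width 5, or 2.5 × √50 / 1.96 = 9.0 for full width 5. The stated SD is 10.

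**Step 2: add the +/- 2 % to the variance (95 %).** This applies only if the SD of 10 excludes measurement error.

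| SD used | Half-width 5 (z / t) | Full width 5 (z / t) |
|---|---|---|
| √(10² + 1.02²) = 10.05 (2 taken as a 95 % limit) | 16 / 18 | 63 / 65 |
| √(10² + 2²) = 10.2 (2 taken as an SD, one measurement) | 16 / 19 | 64 / 67 |
| √(10² + 2 × 2²) = 10.39 (error at both measurements) | 17 / 20 | 67 / 69 |

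If the SD of 10 already describes observed changes, it contains the measurement error and Step 1 stands unaltered.

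**Step 3: routes that come near 50.** Each needs something that the article does not state.

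- Subtract the tool precision from the target, h = 5 − 2 = 3, at 95 %: (1.96 × 10 / 3)² = 42.7, so 43 (t: 46). With SD 10.2 the result is 45 / 47, and with SD 10.39 it is 47 / 49. The last uses the tool error in both the SD and the target.
- Inflate 43 to 47 for 5 to 10 % dropout: 46 to 53.
- 90 % confidence, full width 5, SD 10.39: 47 / 49.
- 99 % confidence, half-width 5, SD 10 + 2 = 12, with 80 to 90 % assurance of the width: 49 to 52.
- A one-sample test of a 5-point change with 95 % power: 52. This is not a precision calculation.

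**Step 4: what 50 children deliver at SD 10.** Half-width at 95 %: 1.96 × 10 / √50 = 2.77 (z), or 2.0096 × 10 / √50 = 2.84 (t). The full width is 5.54 to 5.68. At 90 % the half-width is 2.33 to 2.37 and the full width 4.65 to 4.74.

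The observed SD at which 50 children give exactly +/- 5 (t): 5 × √50 / 2.0096 = 17.6.

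With fewer evaluable children at SD 10 (t): 45 give 2.015 × 10 / √45 = 3.0, and 40 give 2.023 × 10 / √40 = 3.2.

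**Step 5: consequence for small changes.** For an observed mean change of 6 %, the lower limit is 6 − 5 = 1 or 6 − 2.84 = 3.16, so both intervals exclude zero. For 3 % it is 3 − 5 = −2 or 3 − 2.84 = 0.16, so only the narrower interval does, and only just.

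**The case against.** The strongest reply is that the article condenses a fuller protocol, and that the confidence level, dropout allowance and use of the +/- 2 % may be set out there. The tool precision is listed as a separate assumption, and narrowing the target from 5 to 3 brings n to 43 to 49. A modest dropout allowance then gives 50. So 50 may be the rounded result of a method not described here. This stands as an explanation of where the figure may have come from, and the missing details are not themselves the finding. It does not make the figure follow from the inputs as printed. Subtracting a measurement precision from a target half-width is also not a valid way to combine errors.

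Stronger readings are tempting, and the document does not support them:

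- *The stated precision is wrong, or the study is too small.* If 5 % is a half-width, 50 children more than meet it. If it is a full width, the shortfall at 95 % is 0.5 to 0.7 points, and at 90 % the target is met.
- *An interval of +/- 5 would miss the residual change expected at 60 minutes.* The only figure cited at 60 minutes is 6 %, for which +/- 5 still excludes zero. The 3 % figure was measured at 40 minutes.
- *The assumed mean of 20 %, above the adult 15 to 16 %, distorts the size.* The mean has no effect on n here. The comparison is also with adults, and the Background says that nothing is published on CI in children.

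**Conclusion.** The sample size of 50 is not reproducible from the inputs stated for it. At 95 % confidence without dropout they give 16 to 20 children or 62 to 69, depending on whether 5 % is a half-width or a full width and on whether tool error is added. Changing the confidence level to 90 % or 99 % with SD 10 does not produce 50 either.

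The conclusion is about the justification and not about the adequacy of the study. Fifty children with an SD of 10 points give about +/- 2.8 points, which is a useful precision that the article does not report. The result rests on the standard interval for one mean, on 50 evaluable children, and on the SD of 10 holding at both time points. The article supports none of these separately for 60 minutes. Severity: should-fix, because the figure is the basis for the study size but its correction leaves enrolment unchanged.

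**What to change.** Keep enrolment at 50. Remove the statement that 50 is required for a precision of 5 %, and replace it with wording such as:

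> With 50 evaluable children and an SD of 10 points, the expected 95 % confidence interval half-width for mean percentage change in CI is about 2.8 points (3.0 with 45 evaluable, 3.2 with 40). With 50 evaluable it is about 5 points if the observed SD is 17.6.

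Apply this to both the 5- and the 60-minute time points, and mark the SD of 10 at 60 minutes as an assumption. State the confidence level, that precision means half-width, and how the +/- 2 % was used, or that it was not. The figures for 45 and 40 are worth giving because the Limitations section expects ultrasound to be difficult in some children.

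The cost is a reworded paragraph, with no change to enrolment or procedures.
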